### Additional analyses

The center effect will be tested. Intervention-by-subset interactions will be assessed to see whether the impact of the intervention is homogeneous or not in the three following predefined groups of relatives: being a spouse (vs. other relatives), French descent (vs. other origins), and aged over 65 years (vs. under 65). Also, a per protocol analysis will be performed for those relatives from the control group who unexpectantly received at least two of the three components of the intervention.

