### Eligibility criteria

ICUs with ≥8 beds, a ratio of 1/2.5 nurses per patient, and 24 × 7 medical coverage were eligible. Participating centers were selected from (1) the Famiréa network, based on previous and repeated participation in Famiréa studies and (2) a list of centers that had never participated in Famiréa studies. Famiréa is a French research group that aims to study family members’ experience both during and after the patient’s ICU stay to improve practices, specifically communication skills and EOL care. Since its creation 20 years ago, it has promoted research into family-centered care in a network of ICUs that strive to put into practice the findings of published studies.

The study population consists of bereaved family members after the death of an adult patient in an ICU who fulfil all the inclusion criteria and none of the exclusion criteria.

Relatives of patients who meet the following criteria are included: patient >18 years who died in an ICU after a decision to withhold or withdraw treatment and ICU length of stay ≥2 days. To be included, relatives must be available to give consent to participate in the study. Relatives who do not understand, read, or speak French or who refuse to participate are excluded, as well as relatives of organ donor patients (as these relatives benefit from specific support and adapted communication by the transplant coordination teams).

As in previous Famiréa studies [1, 4, 21], only one family member is included. This family representative is the designated health-care proxy. In their absence, this is the family member most involved in the relationship with the ICU team, or by default is the spouse (or partner). In their absence, it is the parents or children of the patient, then another member of the family.

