### Statistical analysis

The hypothesis is that the proactive communication strategy will decrease the proportion of relatives presenting complicated grief symptoms from 50% to 35% 6 months after the patient’s death (assumed decrease). To do so, we need to recruit 454 relatives (227 in each group) to give a power of 90% and a type I error rate α of 0.05. Moreover, given it is a cluster randomized trial, a between-cluster variation must be accounted for, using an inflation factor or design effect of $$ 1+\left(\overline{n}-1\right)\uprho $$, where $$ \overline{n} $$ is the average cluster size and ρ is the intracluster correlation coefficient assuming the clusters are of a similar size [43]. Assuming a small clustering effect (intracluster correlation coefficient = 0.05), with an estimated average recruitment of 25 subjects per cluster, the inflation factor is set at 1.55, resulting in 704 enrolled subjects. As it is expected that 25% of the relatives will be lost to follow-up at 6 months [1, 4, 21], the sample size is increased to 874 (437 in each group).

The analysis will be done according to the intention-to-treat principle (each subject will be analyzed in the group to which they were was assigned by the randomization, regardless of whether or not it was effectively done). Descriptive statistics in each group (means, medians, or percentages as appropriate) will be used to assess any marked differences between the intervention and control groups. Point estimates with 95% confidence intervals will be reported for the primary outcome. This is a cluster randomized controlled trial, with correlation among patients from the same cluster.

The primary and secondary outcomes will be compared across randomized groups at the individual patient level, taking into account the correlation induced by the study design. The intracluster correlation coefficient or *k* statistic for each primary and secondary outcome will provide an indication of the extent of the clustering. Moreover, the correlation will be considered in the statistical analysis of the outcomes using mixed effects models, with both adjusted and unadjusted estimates [43, 44].

Missing data on covariates will use the multiple imputation by chained equation. The scores will be analyzed based on original data, and when available, according to established cutoffs. All tests will be bilateral and significance will be defined as *p* < 0.05.

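### Effect modification by age is tested only through a cut at 65, and the three interaction tests are framed as a yes/no question on homogeneity that this sample size cannot answer

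*Protocol article*

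**What the plan says.** The protocol article, Additional analyses, gives the purpose as follows: "Intervention-by-subset interactions will be assessed to see whether the impact of the intervention is homogeneous or not". The three predefined subsets are "being a spouse (vs. other relatives), French descent (vs. other origins), and aged over 65 years (vs. under 65").

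Statistical analysis sets one rule for every test: "All tests will be bilateral and significance will be defined as" p < 0.05. No separate level or reading rule is given for the interactions. The commitment to 95% confidence intervals in that section is made for the primary outcome.

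For the choice of family representative, Eligibility criteria treats spouse and partner as one role: "or by default is the spouse (or partner"). The subset definition names the spouse only.

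The trial is sized on the assumption that the strategy "will decrease the proportion of relatives presenting complicated grief symptoms from 50% to 35% 6 months after the patient’s death". The article claims no power for the interactions and gives no expected subset shares.

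**The concern.** Age is a continuous variable. Reducing it to two groups discards the variation within each group and so weakens the one test meant to show whether the benefit changes with age. Read literally, the cut also leaves a relative aged exactly 65 in neither group.

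The second issue applies to all three subsets. A test at p < 0.05 can give evidence that effects differ. Failing to reach p < 0.05 is evidence that they are similar only if the interval around the contrast is narrow. If that interval is as wide as the planned treatment effect, the *homogeneous* half of the question has no answer in this trial. At stake is how the subset results are read, not the primary comparison.

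**Working it through.** **Inputs from the article (Statistical analysis).** 50% vs 35%, a 15-point difference; two-sided α = 0.05; power 90%; 874 relatives; 25% lost at 6 months. **Assumed, because the article does not give them:** the subset shares, and that the interaction is measured as a difference of risk differences on the binary outcome used to size the trial.

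**The plan's own figure.** With pooled variance, mean proportion 0.425 and no continuity correction:

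n per group = [1.96 × √(2 × 0.425 × 0.575) + 1.2816 × √(0.25 + 0.2275)]² / 0.15² = (1.370 + 0.886)² / 0.0225 ≈ 226.2, rounded up to 227.

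This reproduces "we need to recruit 454 relatives (227 in each group"), so the event rates and error levels are read correctly.

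**Evaluable sample.** 874 × 0.75 = 655.5, or about 328 per arm.

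**Precision and power of an interaction.** With f the share of relatives in the subset:

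- SE of the overall risk difference = √((0.25 + 0.2275)/328) = 0.0382
- SE of the interaction = 0.0382 / √(f(1 − f))
- Power for a 15-point interaction = 1 − Φ(1.96 − 0.15/SE)
- 95% CI half-width = 1.96 × SE

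| Subset share f | SE | Power | Half-width (points) |
|---|---|---|---|
| 50% | 0.0763 | 50% | 15 |
| 25% | 0.0881 | 40% | 17 |
| 15% | 0.107 | 29% | 21 |
| 10% | 0.127 | 22% | 25 |

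**Clustering.** No design effect is applied here. The subsets are characteristics of individual relatives, so the center effect largely cancels when subsets are compared within centers. A simulation of 36 clusters of 18 evaluable relatives with an intracluster correlation of 0.05 gave power of 51%, 43%, 34% and 19% at shares of 50%, 30%, 20% and 10%, close to the unclustered formula (50%, 44%, 35% and 22%). Applying the article's full inflation factor of 1.55 would lower the 50:50 figure to 35%, so the table leans towards the favorable side.

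**What could be missed, holding the average effect at 15 points.**

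- Equal subsets with effects of 22.5 and 7.5 points differ by 15 points: power about 50%.
- If a 15% subset gets no benefit, the rest get 0.15/0.85 = 17.6 points. Then 0.176/0.107 = 1.65, and power is about 38%.
- If a 25% subset gets no benefit, the rest get 0.15/0.75 = 20 points. Then 0.20/0.0881 = 2.27, and power is about 62%.

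**Cost of the age cut.** For an effect that changes linearly with a normally distributed age, a split with a proportion p above the cut keeps a fraction φ(z)²/(p(1 − p)) of the information, where z is the normal quantile at the cut:

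- p = 0.50: 0.3989²/0.25 = 0.637
- p = 0.25: 0.3178²/0.1875 = 0.539

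Equivalently, the split test needs about 1/0.637 = 1.57 or 1/0.539 = 1.86 times as many relatives as the continuous test for the same power against such a trend.

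**The case against.** The strongest defense is that this is a sound subgroup plan for its purpose. It names only three subsets, fixes them in advance, tests interactions rather than comparing p-values within subsets, and places them under Additional analyses. Low power for interactions is usual in trials sized for a main effect, and the article promises none. All of that stands: low power here is a limit on interpretation, not a design error.

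Several stronger readings are tempting, and the article does not support them:

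- *A non-significant test will be reported as a homogeneous effect.* No sentence says so. The stated aim invites that reading but does not commit to it, and a full protocol or analysis plan may set out the interpretation.
- *Non-significance is likely even if one subset gets no benefit and the other twice the average.* This is wrong. That pattern requires equal subsets and is a 30-point interaction: 0.30/0.0763 = 3.93, with power of about 98%.
- *The age cut weakens all three tests.* It affects the age test only.
- *Leaving out relatives aged exactly 65 costs power.* The loss would be very small; this is a gap in wording.
- *Unmarried partners will be counted with other relatives.* The word spouse is probably shorthand for the combined role used in Eligibility criteria.

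It is also fair to say that the 64% and 54% figures rest on a linear trend and roughly normal ages, neither of which the article documents, and that a prespecified cut is common for display. That argues for keeping the cut in a table, not for making it the only test.

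**Conclusion.** The point holds as a better method at small cost, not as an error that threatens the trial. Under a roughly linear trend in roughly normal age, testing age only through the cut gives up about 36% to 46% of the information on that one interaction. For all three subsets, an interaction as large as the whole planned effect would be detected about half the time at best, and about 22% of the time if the subset is a tenth of the sample. Even in the most favorable case, the interval around an interaction estimate of zero reaches about 15 points in each direction. Homogeneity is therefore not a conclusion these tests can support, whatever their p-values. The power figures depend on subset shares that the article does not state and on 656 evaluable relatives. The primary analysis is not affected.

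**What to change.** - **Age.** Make the interaction test arm-by-age with age continuous, adding a simple non-linear term if needed, and show the fitted effect at several ages. Keep the cut for display only, written *65 or older vs under 65*.
- **Aim and reporting.** Replace the homogeneous-or-not aim with estimation: report the effect in each subset and each interaction contrast with a 95% confidence interval, and state that p ≥ 0.05 is not evidence of homogeneity.
- **Wording.** Write *spouse or partner vs other relatives*, so that the subset matches Eligibility criteria.

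The cost is one extra model, a figure in place of a two-row table for age, and a few lines of text. The continuous age result will depend somewhat on the shape assumed for the trend, so that shape should be fixed before the outcome data are examined.

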### Qualitative analysis

All interviews will be audio-taped and transcribed verbatim. All of the transcripts will be read extensively to gain an overall understanding of participants’ views and experiences. The data will then be analyzed thematically using the grounded theory methodology. Themes are not hypothesized prior to the interviews but will emerge from the respondents’ words. For the data analysis, we will use open, axial, and selective coding. In open coding, researchers categorize the data from the interview transcripts into broad categories or themes. In axial coding, each category is characterized and the relationships between categories are examined. Finally, in selective coding, the categories are organized into a framework to explain a phenomenon.

### Provisional timetable

Altogether, 36 centers (Additional file 1) are participating in the study. Based on the CAESAR study [1], four or five decisions to withhold or withdraw life-sustaining therapies are managed per month by each ICU. Each ICU will recruit 25 relatives. To permit a quality follow-up of the relatives and to avoid researchers being overloaded with follow-up telephone calls, relatives are enrolled in three time periods: centers 1 to 12 recruit during the first 6 months, centers 13 to 25 start during the next 6 months, and centers 26 to 36 during the final 6 months. Hence, recruitment is expected to last approximately 18 months. The follow-up of relatives will last for a total of 24 months.

### Strengths and limitations

The main difficulty in implementing this intervention aimed at improving communication and the attitudes of health-care professionals is adherence to the study protocol, since the strategy we propose concerns all members of the ICU team, including doctors and nurses. However, four strategies have been developed to limit the risk of non-adherence: (1) dissemination of a video presenting the strategy that can been seen at any time by any member of an intervention center, (2) quantitative monitoring of fidelity using a checklist for each inclusion, (3) qualitative monitoring in two ICUs by an outsider observer, and (4) regular interactions between the principal investigator and the local champions in each ICU to discuss difficulties and promote the correct implementation of the strategy.

Our study has several strengths: (1) it is a national study involving 36 ICUs, (2) it has a high number of inclusions, and (3) it is a strategy aimed at improving communication and behavior of doctors and nurses, thus increasing general awareness and changing the EOL culture.

### Data monitoring

The data will be monitored by the Clinical Research Unit of Saint Louis University Hospital. The data will be managed by the Biostatistics and Medical Information Service of Saint Louis University Hospital, Assistance Publique – Hôpitaux de Paris (AP-HP).

## Discussion

This study is focused on relatives of patients who died in an ICU. The psychological burden is extremely high for relatives in this context, with 50% presenting prolonged grief symptoms 6 months after the patient’s death, a prevalence that is 5 times higher than in the general population of bereaved relatives. Prolonged grief and posttraumatic stress symptoms considerably diminish quality of life. Prolonged grief is considered by some specialists as a distinct mental disorder on the grounds that it is a clinically significant form of psychological distress associated with substantial disability. The psychological burden co-occurs with lifestyle and employment disruptions as well as health problems. These will be measured in both groups of relatives so that we can understand any psychological, social, and economic benefits of the intervention.

Finding strategies to lower the psychological burden specific to the ICU setting is a necessity. If the study is positive, this communication strategy could be implemented in all French ICUs to reduce the burden, to help families during the grieving process, and to help reduce the social impacts of prolonged grieving. This intervention is costless and not difficult to implement. If the results are positive, this will be an extraordinary achievement. We will have shown how to reduce the burden during one of the most painful life experiences by improving EOL practices. Introducing this strategy to hospital units with high death rates would be an interesting objective.

### Trial status

The trial is currently recruiting relatives. Recruitment started on 23 February 2017.

## Abbreviations

AP-HP: Assistance Publique – Hôpitaux de Paris
COSMIC: Communication Strategies and Measures in Intensive Care
EOL: End-of-life
HADS: Hospital Anxiety and Depression Scale
ICU: Intensive care unit
IES-R: Impact of Event Scale, Revised
MISS-21: Medical Interview Satisfaction Scale
PG-13: Prolonged Grief 13-item questionnaire
PTSD: Posttraumatic stress disorder
QODD-1: Quality of Dying and Death 1-item questionnaire
